### Recruitment {15}

To achieve adequate participant enrolment to reach target sample size. We will post recruitment advertisements message on WeChat groups of universities in Shanghai and put up the advertisements posters in universities to recruit subjects. Universities are the best strategic places to recruit participants needed for this experiment.

## Assignment of interventions: allocation

### Sequence generation {16a}

This experiment will adopt the method of block randomization. An independent researcher who is not in contact with the participants will use the software SPSS23.0 to generate a random number table to divide the 116 eligible participants into an acupuncture group and sham acupuncture group with a 1:1 ratio.

### Concealment mechanism {16b}

After the sequence number is generated, the researcher will make allocation cards and seal each card in an opaque envelope. The envelope will be kept by the same researcher responsible for sequence generation.

### Implementation {16c}

An independent researcher that is blinded to the study protocol will generate the allocation sequence. According to the timing sequence of the participant registration for the trial, another researcher will arrange the participants into different groups and inform the acupuncturists of the group assignments.

## Assignment of interventions: blinding

### Who will be blinded {17a}

This is a single-blinded (participants-assessor-blinded) trial. Participants will be asked to wear an eye mask during the whole intervention in an enclosed space. All researchers except the acupuncturists and sonographer will be blind to the group assignment, including statisticians, outcome assessors, and data analysts. We will attempt to validate the successful implementation of the blinding method. All participants will be told that the presence or absence of acupuncture sensation is normal. Furthermore, all researchers will accept training on the RCT specification before the trial and will strictly adhere to the separation principle of each department.

### Procedure for unblinding if needed {17b}

Unmasking is not needed. If a participant asks to be unblinded out of curiosity rather than the adverse reactions because of intervention, he or she will be informed of the group allocation after the trial.

## Data collection and management

### Plans for assessment and collection of outcomes {18a}

The measurement and collection of this study’s outcomes include ultrasound observation video of antral motility, ultrasonic image of ST36, and infrared chart of stomach before and after acupuncture. ACF, ACA, and AMI are the three indicators of antral motility, which will be continuous monitoring by ultrasound diagnostic equipment to ensure that there is sufficient playback data for analysis.

#### Plans to promote participant retention and complete follow-up {18b}

Follow-up of subjects is not required in this study. This trial is an observation of the immediate effects of acupuncture intervention without involving any longer follow-up evaluation. We will collect ultrasound and infrared thermal imaging data before and after acupuncture intervention. Although participants who do not receive needling for any reason, their ultrasonic data of gastric antrum will also be collected, because we need to use ultrasound imaging technology to help determine whether the participants meet the inclusion criteria.

### Data management {19}

We will use a clinical trial management platform called ResMan to manage the original data, which will be collected and double-entered by blinded assessor. The data management system will be tested before the officially launched and will be protected by password. The original data of participant will be entered within 1 week after finishing the trial. Data supervisor will check every trial data at least once a month to make sure that they will be recorded accurately, timely, and completely.

### Confidentiality {27}

This protocol, CRFs, and other documents and materials related to the study will be kept strictly confidential and will not be disclosed to third parties except with the consent of the Principal Investigator. Any public report on this study will not disclose the subjects’ personal identity, and we will make every effort to protect the privacy of participants’ personal medical information within the sphere permitted by law. The staff in this study is also bound by this agreement.

### Plans for collection, laboratory evaluation, and storage of biological specimens for genetic or molecular analysis in this trial/future use {33}

Not applicable, this trial does not have biological specimens.

## Statistical methods

### Statistical methods for primary and secondary outcomes {20a}

Data analyses will be performed with the statistical software SPSS23.0 by an independent statistician. The analysis will include an intention-to-treat(ITT) analysis, including data for all participants who dropped out of the trial. Descriptive statistical analysis will be used for all demographic and clinical characteristics of subjects such as sex, age, and weight. We will validate the homogeneity of demographic characteristics and examine the variables between the 2 groups. The mean ± standard deviation will be used for description of the continuous variables. Qualitative data will be expressed in terms of frequency and percentage.  Student's t-test will be used to compare the measurement data between the 2 groups. Rank-sum test is used for ranked data, while the chi-squared test is adopted to analyze categorical data. The significance level used for statistical analysis with 2-tailed testing will be 5%.

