**Methods:**

This is a two-arm, single-blind, randomized, controlled trial. A total of 116 acupuncture-naïve healthy subjects will be randomly allocated to the acupuncture group or sham acupuncture group in a 1:1 ratio. Participants in the acupuncture group will receive manual acupuncture at Zusanli (ST36) with the needling depth at crural interosseous membrane. Those in the sham acupuncture group will be given penetrating needling depth at the superficial fascia layer. The primary outcome will be the changes in antral contraction frequency (ACF) before and after acupuncture. The secondary outcomes will be the changes in the thermal infrared spectrum of gastric area skin, the antral contraction amplitude (ACA), the antral movement index (AMI), and the scores on the Chinese version of Massachusetts General Hospital Acupuncture Sensation Scale (C-MASS). The adverse events will be evaluated and recorded in detail.

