#### Sham acupuncture group

Participants in the sham acupuncture group will be punctured at ST36 with the needle tip reaching no deeper than the superficial fascia and without any needle manipulations. The remaining procedures and recording details are the same as those of the acupuncture group.

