### Primary outcome

Antral contraction frequency (ACF) is the primary outcome of this study. The ultrasound probe will be placed vertically to simultaneously obtain the image of gastric antrum, superior mesenteric artery, abdominal aorta, and left lobe of the liver. ACF will be recorded for 10 min before and after the continuous needling. Frequency of antral contractions = number of contractions per 10-min period.

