### Sample size {14}

The sample size was estimated using the Power Analysis and Sample Size (PASS version 15) software. According to our pilot trial, we anticipate that the change in the frequency of antral contraction will be more pronounced in the acupuncture group than in the sham acupuncture group and that we will detect a difference of 30% between effective rates in the 2 groups (70% in the acupuncture group compared with 40% in the sham acupuncture group). On the basis of a 2-sided alpha level of 0.05 and a power level of 90% with a 10% dropout rate, we calculated that our trial will require a sample of 116 participants (58 in each group).

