### Methods for additional analyses (e.g., subgroup analyses) {20b}

Not applicable. The trial has no plan for additional analyses.

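### The ACF comparison, most likely a change-score t-test, does not adjust for baseline ACF; ANCOVA would be more precise and needs no extra data

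*Protocol article*

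**What the plan says.** The protocol article fixes the test for continuous outcomes in Statistical methods for primary and secondary outcomes {20a}: Student's "t-test will be used to compare the measurement data between the 2 groups". No model and no covariate are named there. The section on additional analyses {20b} adds that "The trial has no plan for additional analyses".

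The abstract states: "The primary outcome will be the changes in antral contraction frequency (ACF) before and after acupuncture". The Primary outcome section says that "ACF will be recorded for 10 min before and after the continuous needling" and defines frequency as a count per 10-minute period. The acupuncture arm's procedure includes a 10-minute ultrasound recording before the needle goes in. For the sham arm, "The remaining procedures and recording details are the same as those of the acupuncture group". Baseline ACF is therefore measured in both arms.

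The only mention of comparability in {20a} is this: "We will validate the homogeneity of demographic characteristics and examine the variables between the 2 groups". No adjustment of the treatment comparison follows from it.

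**The concern.** In a randomised trial with one measurement before and one after the intervention, the baseline value is usually a useful predictor of the later one. A change-score t-test subtracts the baseline in full, as if the slope of post on pre were exactly 1. When the pre-post correlation is below 1 (with equal variances), that over-corrects. It adds variance, and an arm that starts high by chance is expected to fall more for that reason alone. ANCOVA estimates the slope from the data and avoids both problems.

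At stake is precision, together with protection of this one trial's estimate against a chance difference in baseline ACF. The homogeneity check in {20a} may reveal such a difference but does nothing to the treatment estimate.

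**Working it through.** **The plan's own figure.** Sample size {14} assumes "70% in the acupuncture group compared with 40% in the sham acupuncture group", "On the basis of a 2-sided alpha level of 0.05", 90% power and 10% dropout, and gives 116 (58 per arm). The two-proportion formula with unpooled variance gives

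n = (0.7×0.3 + 0.4×0.6) × (1.960 + 1.282)² / 0.30² = 52.5 per arm.

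Dividing by 0.9 gives 58.4; rounding up to 53 first and then inflating gives 59. The total is 116 to 118, so the stated number is reproduced to within 2 participants. It rests on effective rates and not on mean ACF, so it neither supports nor depends on what follows.

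**Inputs for the comparison of methods.**
- Arms of 58, from {14}. The intention-to-treat rule in {20a} and {20c} keeps dropouts in, with baseline values substituted, so 58 and not 52 per arm is the analysed number.
- Pre-post correlation ρ: not given. Assumed, and shown from 0.3 to 0.9.
- Equal variance before and after needling: assumed.

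**Variance of the treatment difference**, relative to a t-test on the post value alone:
- t-test on change: 2(1−ρ)
- ANCOVA: 1−ρ²
- ANCOVA relative to change: (1−ρ)(1+ρ) / [2(1−ρ)] = (1+ρ)/2, which is below 1 whenever ρ < 1.

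**Illustrative power.** Take an effect that the change-score t-test would detect with 90% power, two-sided 5%. Power with ANCOVA is Φ[(1.960 + 1.282)/√((1+ρ)/2) − 1.960]. For ρ = 0.5 this is Φ(3.242/0.866 − 1.960) = Φ(1.78) = 0.963.

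| ρ | Variance ratio (1+ρ)/2 | ANCOVA n per arm matching a change-score t-test with 58 | Power if the change-score t-test has 90% |
|---|---|---|---|
| 0.3 | 0.65 | 38 | 98.0% |
| 0.5 | 0.75 | 44 | 96.3% |
| 0.7 | 0.85 | 50 | 94.0% |
| 0.9 | 0.95 | 56 | 91.4% |

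The third column is 58 × (1+ρ)/2, rounded up. These are large-sample results. Estimating the slope costs ANCOVA one degree of freedom (113 instead of 114 with 116 participants), which is negligible.

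**Chance imbalance.** With 58 per arm, the baseline difference between arms has standard error √(2/58) = 0.186 SD, so its 95% range is about ±1.96 × 0.186 = ±0.36 SD. Given a baseline difference δ, the change-score estimate shifts by −(1−ρ)δ. For δ = 0.2 SD the shift is −0.14, −0.10, −0.06 and −0.02 SD at ρ = 0.3, 0.5, 0.7 and 0.9. ANCOVA removes this shift in expectation.

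**The case against.** The strongest reply is that this is an efficiency choice and not an error. A change-score t-test in a 1:1 randomised trial keeps its type I error and is unbiased on average, and it already uses the baseline by subtracting it. Covariate adjustment is often left to a statistical analysis plan, and this is a condensed article. The first part stands in full. The second stands only in part: the article is not silent, since it names the test for measurement data and says that no additional analyses are planned.

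The size of the gain is also open to challenge. The two ultrasound recordings are made in one session, with only the needling between them, so a high correlation is plausible and the gain could be small. That stands, and it is why the table runs to 0.9.

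Three stronger readings are tempting and are not supported:
- A reader might infer that baseline is ignored altogether. On a post-value t-test the ANCOVA variance ratio would be 1−ρ² (0.91, 0.75, 0.51 at ρ = 0.3, 0.5, 0.7). But the abstract defines the outcome as change, so this is the less likely reading.
- A reader might take the table as the trial's own power rising from 90%. The article gives no ACF standard deviation and no mean difference. Its 90% refers to effective rates, and the 90% starting point used here is only illustrative.
- A reader might infer that the homogeneity check is a significance test of baseline ACF offered in place of adjustment. The text speaks of demographic characteristics and variables, names no test for this purpose, and makes no such claim.

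Finally, no sentence ties the t-test to ACF by name. An effective rate would go to the chi-squared test. That mismatch between sample size and outcome is real but separate.

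**Conclusion.** The point holds as a recommendation on precision. It does not make the planned analysis invalid. On the likely reading, the ACF comparison is a change-score t-test: sound over randomisation, but less efficient than baseline-adjusted ANCOVA for any correlation below 1, and exposed to chance imbalance in a baseline that every participant provides. Under equal pre and post variance, the saving in variance runs from 35% at a correlation of 0.3 to 5% at 0.9. Where in that range the trial lies cannot be told from the article. The direction of the gain is secure; its size is an assumption. The change is worth making because it takes so little, even if the gain proves small.

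**What to change.** In {20a}, name the analysis of ACF as ANCOVA of post-needling ACF (or its change) on arm and baseline ACF, reporting the adjusted mean difference in contractions per 10 minutes with its 95% CI. With baseline in the model, the arm effect is the same whether the dependent variable is the post value or the change, so the choice between the two no longer matters. Use the same model, each with its own baseline, for antral contraction amplitude, antral motility index and abdominal skin temperature. Keep the t-test as a supportive analysis.

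The cost is one or two sentences, fixed before unblinding. SPSS 23.0 fits the model, and no further data or participants are needed. The change does not settle the mismatch between a sample size based on effective rates and an outcome analysed as a mean, which needs its own correction.

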### Interim analyses {21b}

Not applicable. Interim analyses will not be performed in this study.

### Methods for additional analyses (e.g., subgroup analyses) {20b}

Not applicable. The trial has no plan for additional analyses.

### Methods in analysis to handle protocol non-adherence and any statistical methods to handle missing data {20c}

All data in this study will be analyzed according to the principle of ITT to reduce deviation, including the subjects who withdraw from the study during the study period. The missing data will be substituted into the subjects’ baseline data for final data analysis.

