### Criteria for discontinuing or modifying allocated interventions {11b}

The sonographer of this study will perform an ultrasound examination of the stomach before the trial to make sure there are no pathologic changes in the stomach. The trial will be discontinued if one of the following situations occurs: a large amount of gas in the gastrointestinal tract that affected the ultrasonic observation, which can result in collecting and analyzing data difficultly, and participants who have acupuncture-related serious adverse reactions during the experiment or failure to complete the study for any other reasons. We will record the details in the report for the early termination of the study.

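### Substituting baseline for missing values records zero change in antral contraction frequency as if observed, biases the comparison when loss differs by arm, and conflicts with the dropout allowance in the sample size

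*Protocol article*

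**What the plan says.** The section on non-adherence and missing data {20c} gives the analysis set and one missing-data rule. On the set: "All data in this study will be analyzed according to the principle of ITT to reduce deviation, including the subjects who withdraw from the study". On missing values: "The missing data will be substituted into the subjects’ baseline data for final data analysis". The wording is awkward, but baseline carried forward is the only sensible reading. No other method is given there, and the section on additional analyses {20b} says none are planned.

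The abstract defines the primary outcome as the change in ACF from before to after needling. The statistical methods section {20a} assigns Student's t-test to measurement data.

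The sample size section {14} uses effective rates of "70% in the acupuncture group compared with 40% in the sham acupuncture group". From these, with a two-sided alpha of 0.05, 90% power and an allowance of 10% for dropout, it arrives at 116 participants, 58 per arm.

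The discontinuation section {11b} names, without ranking them, "a large amount of gas in the gastrointestinal tract that affected the ultrasonic observation", serious acupuncture-related reactions, and failure to finish for any other reason.

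**The concern.** For a change score, carrying the baseline forward is a claim about the participant: that ACF did not move at all. The analysis then treats that claim as a measurement. None of the listed reasons for stopping supports it. Gas that hides the antrum is an imaging failure and carries no information that contraction frequency stayed the same. If gas also spoils the baseline recording, there is nothing to substitute.

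Loss could plausibly differ by arm. One arm receives deep needling with manipulation and the other a superficial insertion without it; participants have never had acupuncture; and the sonographer, who knows the allocation {17a}, acquires the images. At stake are the size and direction of the primary estimate, its error rate, and whether the stated power holds under the analysis that will be run.

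**Working it through.** **Inputs from the protocol article.** Rates 0.70 and 0.40, two-sided alpha 0.05, power 90%, dropout 10%, 58 per arm {14}; baseline substitution in an ITT set {20c}.

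**Inputs assumed.** The split of loss by arm; that zero change counts as not effective; the session drift; an SD of change of 1.

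**1. The plan's own figure.** Unpooled two-proportion formula: n = (1.960 + 1.282)² × (0.7×0.3 + 0.4×0.6) / 0.30² = 52.5 per arm. Then 52.5 × 1.1 = 57.8, or 52.5 / 0.9 = 58.4. The stated 58 per arm is reproduced to within rounding. The pooled formula gives 56 per arm, or 63 after dropout, and does not match. The allowance makes sense only if dropouts leave about 52 per arm analysed (58 × 0.9 = 52.2).

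**2. Sizing endpoint under the rule, 10% loss in each arm.** The rates become 0.9 × 0.70 = 0.63 and 0.9 × 0.40 = 0.36, so the difference falls from 0.30 to 0.27. All 58 per arm are analysed.

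- Unpooled: 0.27 / √[(0.63×0.37 + 0.36×0.64)/58] − 1.960 = 1.06, power 85.6%.
- Pooled: 83.8%. Exact chi-squared without continuity correction: 84.0%.

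The like-for-like comparison is dropouts simply leaving (52 per arm, 0.70 v 0.40):

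| Method | Dropouts leave | Baseline substituted |
|---|---|---|
| Unpooled | 89.7% | 85.6% |
| Pooled | 87.9% | 83.8% |
| Exact | 89.5% | 84.0% |

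The rule itself therefore costs about 4 to 5.5 points. At 5% loss per arm the rates are 0.665 and 0.38, and power is 87.7% (pooled) or 89.4% (unpooled). Holding 90% under the rule at 10% loss would take 67 (unpooled) to 70 (pooled) per arm.

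**3. Unequal loss, same 10% overall, sizing endpoint.** With 15% acupuncture and 5% sham: 0.85×0.70 − 0.95×0.40 = 0.215, power 64% to 66%. Reversed: 0.95×0.70 − 0.85×0.40 = 0.325, power 95% to 96%, with the difference overstated.

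**4. Change in ACF.** Let m_A and m_S be the mean changes and q_A and q_S the missing fractions in the acupuncture and sham arms, with missingness unrelated to outcome. The expected difference under the rule is (1 − q_A)m_A − (1 − q_S)m_S.

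- Equal loss q gives (1 − q)(m_A − m_S). At 10%, 0.64 SD becomes 0.58 SD. (0.64 SD is what 52 per arm detects with 90% power: 3.242 × √(2/52).)
- No effect, common drift 1 SD, 15% v 5% missing: 0.85 − 0.95 = −0.10 SD; simulated type I error 8.6%.
- No effect, drift 0.5 SD, 15% v 5%: −0.05 SD; 5.9%.
- Effect 0.64 SD, drift 0.5 SD, 15% v 5%: 0.85×1.14 − 0.95×0.50 = 0.49 SD; power 76%.
- Same with 5% v 15%: 0.95×1.14 − 0.85×0.50 = 0.66 SD; power 95%.
- Effect 0.64 SD, 10% missing in each arm: t-test power about 89% with no drift, 88% at 0.5 SD and 85% at 1 SD.

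**5. Where the rule cannot be applied.** The C-MASS is completed only at the end of the session {12}, so it has no baseline value.

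**The case against.** The strongest reply is that the practical loss is small. The trial is one session without follow-up {18b}, so missingness may be well under 10%. With equal loss there is no type I inflation, and power for a t-test on change stays at about 84% to 90% for drifts up to 1 SD. The article gives no drift, SD or unequal loss, so the bias figures are illustrative. At 7% v 3% missing the type I error is only 5.2% (0.5 SD drift) to 5.6% (1 SD). All of this stands, and it limits the severity.

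Some stronger readings are tempting but not supported:

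- That the plan's own inputs put power at 84%. That figure also needs equal loss by arm and zero change counted as not effective, and the article states neither. The formula that reproduces 116 gives about 86%.
- That the rule always shrinks the effect. Enough extra loss in the sham arm inflates it.
- That gas is the main expected cause of loss. The article ranks no cause.
- That participants are randomised before the baseline scan. The implementation section {16c} says only that assignment follows order: "According to the timing sequence of the participant registration for the trial". It does not place assignment before or after the recording.

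What the reply does not answer is the rule itself. It is stated in the protocol as the only method, so an unseen analysis plan does not remove it, and low missingness makes it less harmful without making it right.

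**Conclusion.** The point holds. Baseline substitution is the wrong primary rule for a change outcome, and it does not match the dropout allowance behind the 116.

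- **Certain from the text:** missing post-needling ACF is scored as zero change; those participants stay in the analysis; the sample size was inflated as though they leave.
- **Size on the sizing endpoint:** about 84% to 86% power against the stated 90%, if loss is 10% in each arm and zero change is not effective; 88% to 89% at 5% loss.
- **Size for the t-test on change:** a smaller cost with equal loss.
- **Bias:** in either direction with unequal loss. A spurious difference with no treatment effect requires both a common drift and unequal loss. At 15% v 5% missing it is about −0.05 SD with 6% type I error (0.5 SD drift) to −0.10 SD with 9% (1 SD drift).

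This should be fixed. It does not by itself invalidate the trial, because loss in a single session may be low.

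**What to change.** In {20c}, remove baseline substitution from the primary analysis. Compare participants by allocated arm on observed post-needling ACF, with baseline ACF as a covariate. State the assumption: this is valid if missingness is unrelated to outcome given arm and baseline. Add multiple imputation by arm, including all randomised participants, as a sensitivity analysis; keep baseline substitution at most as a further one. Amend {20b}, which now says no additional analyses are planned, and say that the C-MASS has no baseline to carry forward.

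Optionally, state in {16c} that the envelope is opened only after a readable baseline antral recording. The intervention description {11a} already places that recording before needling, so unscannable participants would become screen failures instead of randomised losses.

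The cost is a few sentences and a little more analysis. The primary model would use only participants with data, about 104 at 10% loss (116 × 0.9 = 104.4). It is therefore a complete-case analysis and should be described as such, but the sample size already allows for that number.
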